##### Secondary purpose

##### The efficacy of the study will be further evaluated by comparing the changes in scores on the Visual Analog Scale of coldhypersensitivity in the hands and feet, body temperature (thermometer measurement), Quality of Life Assessment Questionnaire (WHOQOL-BREF), Quality of Life Assessment EQ-5D, pattern identification questionnaire, and coldness diagnostic questionnaire between the no-treatment control group, acupuncture treatment group, and electro-acupuncture treatment group.

##### Safety assessment

Safety is assessed through adverse events, clinical laboratory tests, and medical examinations.

[figure not shown]

#### About for acupuncture treatments

##### Acupuncture points

###### Acupuncture and electroacupuncture groups

- 1. Hegu (LI4)

Location: On the dorsum of the hand, radial to the midpoint of the 2nd metacarpal bone

[figure not shown]
Efficacy: Relieving fever, dispersing wind, clearing away wind, clearing lung-qi, relieving digestive distress, pain and tranquilizing the mind

- 1. Waiguan (TE5)

Location: On the posterior aspect of the forearm, midpoint of the interosseous space between the radius and the ulna, 2 B-cun proximal to the dorsal wrist crease

Efficacy: Clearing heat and detoxifying, invigorating qi, removing congestion heat from triple energizer meridian

- 1. Taichong (LR3)

[figure not shown]
Location: On the dorsum of the foot, between the first and second metatarsal bones, in the depression distal to the junction of the bases of the two bones, over the dorsalis pedis artery

Efficacy: Extinguish liver fire and triple energizer meridian, regulating liver Qi, promoting blood circulation

- 1.
[figure not shown]
Sanyinjiao (SP6)

Location: On the tibial aspect of the leg, posterior to the medial border of the tibia, 3 B-cun superior to the prominence of the medial malleolus.

Efficacy: Strengthening the spleen, promoting circulation, clearing stagnation of Qi, circulating and regulating the blood, dispelling wind-dampness for the meridians

##### B. Needles, electroacupuncture devices, and treatments used in clinical trials

###### Needle type

0.20 × 30 mm sterile needle (Dongbang Medical, South Korea)

###### Packaging, labeling, and storage

Single-use, sealed, stored at room temperature in the clinical center

###### Clinical trial electroacupuncture devices

The electrospinning machine utilizes an STN-330 (Stratech, South Korea). Details in Appendix.

###### How to use the electrostat

- Prepare

1. Connect the power cord on the back of the main unit to a power source, and turn on the main switch.
2. Confirm that all output dials are set to "0" and that the instrument is operating normally.

- When performing electroacupuncture stimulation.

1. Verify that the dedicated connecting wires used to connect the electroacupuncture devices are free of any cosmetic damage that would cause the sheath to peel off, and that each wire has a dedicated red and black clip attached to it.
2. Securely connect the dedicated connection wire to the output of the electroacupuncture devices (electroacupuncture device cord).
3. Attach the dedicated red and black clips on a dedicated connection wire to connect to the sterile needle.
4. Press the power switch, then set the desired Hz, time, or program.
5. Slowly turn the valve switch to adjust the treatment to the appropriate level of intensity for the patient.

[figure not shown]

[figure not shown]

[figure not shown]

Figure 1. Electroacupuncture device (STN 330) Specifications and Manufacturing License

###### Electroacupuncture Stimulation Methods

- 1. Electroacupuncture stimulation:
     - The acupuncture treatment group consists of 8 points on the bilateral Taichong (LR3), Sanyinjiao (SP6), Hegu (LI4), and Waiguan (TE5), needled at a depth of 10 to 25 mm subcutaneously, and left for 15 minutes. Do not use an electroacupuncture machine.
     - The electroacupuncture treatment group is composed of 8 points on the bilateral Taichong (LR3), Sanyinjiao (SP6), Hegu (LI4), and Waiguan (TE5), needled at a depth of 10 to 25 mm subcutaneously. The Taichong (LR3) is connected to the Sanyinjiao(SP6), and the Hegu (LI4) is connected to the Waiguan (TE5) with a dedicated clip connected to the electroacupuncture needle (red and black color without distinction).
     - Press the power switch of the electroacupuncture device, set the frequency to 2 Hz and the stimulation time to 15 minutes in the on-screen settings, and slowly turn the switches of the individual connecting wires to the right to adjust the intensity to an appropriate level that does not cause pain to the patient.
     - The frequency of treatment is twice a week for a total of 10 acupuncture sessions for 5 weeks, along with electroacupuncture treatment.

##### C. Acupuncture precautions

Care should be taken during acupuncture treatment as it can cause pain, blood clots, tingling sensation, etc.

#### Inclusion/exclusion criteria and the number of participants targeted and their rationale

##### Selection Criteria

It must meet all of the following criteria

1. Women between the ages of 19 and 59 with coldhypersensitivity in the hands and feet
2. Women who meet the definition below, and at least one of the scope items
   - - 1. Definition: A person who complains of discomfort due to cold hands and feet.
       2. Scope items

First, experience coldhypersensitivity in the hands and feet at temperatures where you would not normally feel cold

Second, experience excessive cold extremities compared to others around you at temperatures that make you feel cold

Third, symptoms do not recover easily when moving from a cold to a warm environment

1. Visual Analog Scale (VAS) of 4 or greater for coldhypersensitivity in the hands and feet at the time of the screening visit
2. At the time of screening visit, after 10 minutes of room temperature acclimatization to 24℃ (±2) in the upper and lower exterimities, measured by a thermometer, the temperature difference between the palm (PC8) and arm (LU4) is greater than or equal to 0.3℃, or the temperature difference between the center of the anterior thigh (ST32) and dorsum of the foot (LR3) is greater than or equal to 2℃
3. Who can be followed during clinical trials
4. Agree to participate and sign an informed consent form after receiving a clear explanation of the purpose and nature of this clinical study

##### B. Exclusion Criteria

Individuals who have any of the following conditions are not eligible to participate in this study

1. Taking calcium antagonists or beta-blockers for the treatment of coldhypersensitivity
2. Having one or more ulcers or gangrene on fingers
3. Diagnosed with hypothyroidism or taking thyroid medications
4. Diagnosed with an autoimmune disease
5. Having been diagnosed with carpal tunnel or tarsal tunnel syndrome, or have a positive phalen-tinel test
6. Diagnosed with a herniated disc in the cervical or lumbar spine
7. Diagnosed with diabetes
8. Taking medications that may affect hand and foot coldness (e.g., anticoagulants)
9. Patients with severe hepatic disease (AST-ALT >100 IU/L each) or renal failure (Creatinine >2.0 mg/dL)
10. Behavioral disorders or depression, anxiety, and serious psychiatric disorders
11. Adult women (non-pregnant) Hemoglobin less than 7 g/dL, WBC greater than 11,000/mm^3^
12. Average systolic blood pressure of 180 mm Hg or diastolic blood pressure of 100 mm Hg or higher, measured twice
13. Having a heart condition, such as arrhythmia or ischemic heart disease, that requires treatment on an electrocardiogram
14. Alcohol or drug abusers
15. Pregnant (positive urinary hCG), nursing mothers, women of childbearing potential who are planning to become pregnant or who do not agree to use adequate contraception
16. Having been diagnosed with or treated for a malignancy
17. Participating in another clinical study or within 2 months of completing a clinical study
18. Refused to participate in a clinical trial or provide informed consent
19. Those with limited ability to understand or express Korean
20. Anyone who, in the judgment of the investigator, is deemed unsuitable for the study

##### C. Number of participants

1. Targeted number of participants

|  | Acupuncture  group | Electroacupuncture  group | No treatment group  (control group) | Total number of participants |
| --- | --- | --- | --- | --- |
| Number of eligible evaluations | 18 | 18 | 18 | 54 |
| Number of people considering a  25% dropout rate | 24 | 24 | 24 | 72 |

1. Calculation Rationale

This study was designed to test the hypothesis that acupuncture treatment of patients with coldhypersensitivity in the hands and feet will improve symptoms in the acupuncture treatment group and the electroacupuncture treatment group compared to the no-treatment control group.

The hypothesis of this study is below

H0 : σ = Δ1 – Δ2 = 0

H1 : σ = Δ1 – Δ2 ≠ 0

H0 : σ = Δ1 – Δ3 = 0

H1 : σ = Δ1 – Δ3 ≠ 0

Δ1: Mean change in VAS score from pre-treatment to post-treatment in acupuncture group

Mean change in VAS score of coldhypersensitivity in the hands and feet at week 10 (within ±3 days) after randomization in the acupuncture group

Δ2: Mean change in VAS score from pre- treatment to post-treatment in the electroacupuncture group

Mean change in VAS score of hand coldness at week 10 (within ±3 days) after randomization in the electroacupuncture group

Δ3: Mean change in VAS score from pre-treatment to post-treatment in untreated control group

Mean change in VAS score of hand coldness at week 10 (within ±3 days) after randomization in the no-treatment group

A clinical trial of coldhypersensitivity in the hands and feet with medical devices, acupuncture and electroacupuncture, are designed to estimate the number of participants based on the VAS information form the oxygen chamber device trial.

[figure not shown]
In the referenced trial by Ha et al., the mean VAS difference for the placebo group was -0.48 with a standard deviation of 1.03, and the mean VAS difference for the oxygen chamber group was -1.52 with a standard deviation of 1.17. The expected difference between acupuncture treatments for coldhypersensitivity in the hands and feet is 1.04, and the standard deviation is estimated to be 1.102 using the joint standard deviation formula.

Figure 1. Joint Standard Deviation Formula

The significance level (α), the probabiiity of committing a TypeⅠerror, was set at 0.05, and the probability of committing a TypeⅡerror (β) was assumed to be 0.2. The number of participants in the electroacupuncture treatment group and the no-treatment control group was set to be the same, and the formula for estimating the number of participants by comparing the mean of the two groups was as follows.

[figure not shown]

N = [2*(1.96+0.84)^2*1.17^2]/(1.04)^2=17.625 ≒ 18

Based on the above, the number of participants is 18 in each arm. Considering a 25% dropout rate, 24 participants will be enrolled per arm.

18 ÷ (1-0.25) =24

Therefore, we plan to enroll 24 participants in each of the acupuncture treatment group, electroacupuncture treatment group, and no-treatment control group for a total of 72 participants to be analysed.

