| Concomitant Medications /Therapi es | 1. No new medications are administered during the trial 2. However, they may be administered as needed at the discretion of the investigator. Participants will be excluded if they are taking any medications that, in the opinion of the investigator, may affect the endpoints of this study (e.g., antithrombotic agents (including antiplatelet agents and anticoagulants), psychotropic medications, antidepressant medications, medications related to hyperthyroidism, dietary supplements (red ginseng), OTC blood flow enhancers, medications that may affect tarsal tunnel, etc.) 3. Participants must not take any additional medications during the study period, including Example) Antithrombotic medications (including antiplatelet and anticoagulant medications), psychotropic medications, antidepressant medications, medications related to hyperthyroidism, dietary supplements (red ginseng), OTC blood flow enhancers, and medications that have the potential to affect tingling feet. |
| --- | --- |
| Methods | [figure not shown]  This study is a randomized, multicenter, parallel design, clinical trial. All participants in this study will be fully informed, signed informed consent, assigned a study box identification code, and randomized to one of three arms: no-treatment control, acupuncture treatment, or electroacupuncture treatment. Each participant will visit each study site 10 times, including a screening visit, randomization, and then twice a week for a total of 10 visits. This is a total of 12 visits including screening. The study duration is 5 weeks, with a follow-up visit 4 weeks after the end of the study. |
| Treatment adherence | Drop out if adherence to acupuncture treatment is less than 70% out of 10 visits. |
| Validation methods | 1. Primary outcome variable:   Visual Analog Scale (VAS) of coldhypersensitivity in the hands  Visual Analog Scale (VAS) of coldhypersensitivity in the feet   1. Secodary outcome variable:   (1) Body temperature: Thermometer measurement  (2) Pattern Identification Questionnaire, Coldness Diagnostic Questionnaire  (3) Quality of Life Questionnaire (WHOQOL-BREF) |
| Evaluation of safety | Vital Signs (at every visit), Hematology (WBC, RBC, Hemoglobin, platelet), Blood Biochemistry (BUN, Creatinine, AST, ALT, r-GTP) (at the end of trial)  Safety will be evaluated based on the results of the investigator's examination, adverse event monitoring, and clinicopathologic examination |

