##### Randomization Methods and Blinding

- - 1. Overview

After the particioants have signed the informed consent form, they will be randomized to the acupuncture treatment group, the electroacupuncture treatment group, or the no-treatment control group at Visit 1, if they are deemed eligible for the study after reviewing the inclusion and exclusion criteria. Participants will be instructed on the procedures and visit dates, and will receive 10 treatments twice a week for 5 weeks (±3 days) according to the study schedule. All three arms will be assessed for efficacy 5 weeks (±3 days) after randomization and followed up at 9 weeks (±3 days).

- - 1. Randomization and stratification methods

Patients who agree to participate in this study will be assigned a screening number in the order of their written consent, and if more than one person is screened on a single day, the screening numbers will be assigned in the order of their consent. Randomization codes will be provided by an independent statistician or a third independent investigator with a 1:1:1 ratio of acupuncture, electroacupuncture, and no-treatment control groups. Randomization numbers will be generated using the blockrand package in R 3.4.2 or later, stratified by site at randomization, and block randomization will be used to ensure that the number of participants in each arm is approximately equal. At each site, participants will be assigned numbers based on the order of screening completion.

- - 1. Assignments

This study will use the sealed envelope method. The independent statistician or third independent investigator who generated the randomization code will place a piece of paper with the randomization code inside the opaque envelope, seal it, and give it to the authorized representative at each site. If a participant who has given written consent passes the screening assessment, the authorized representative will open the envelope in the order in which the screening assessment is completed, verify and record the participant's randomization code and assignment arm.

- - 1. Blindfold

This study is an open-label trial in which all arm assignments are not blinded to outcomes. However, we will blind the assessors who evaluate participants' symptoms separately from the treating physician to minimize possible bias in the assessment.

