#### Statistical Methods

##### General principles

The basic analysis method is the degree of change between the results of the baseline test performed before the clinical trial and the results of the test performed at the end of the clinical trial for the efficacy evaluation indicators, and the significance level is 0.05 by two-sided test.

For the efficacy portion of the study, all data from study participants will be analysed using both an intention-to-treat analysis (ITT), in which all participants who met the inclusion/exclusion criteria and who voluntarily agreed to participate in the human study and were randomized regardless of protocol violations or dropouts, and a per-protocol analysis (PP), in which all participants who were randomized will be included in the analysis, excluding participants with noncompliance or missing data. Missing observations for efficacy endpoints will be analysed using the last observation carried forward (LOCF) method, and missing observations for safety endpoints will be treated as missing.

As assigned analyses include all participants who have completed the baseline and final examinations, with the last examination data considered the final examination data. The safety analysis methodology will also follow the as assigned analysis methodology. As-treated analyses will include patients who completed the final examination with no major protocol violations.

The results of the two analyses should theoretically agree within the same study, but if there is an induced difference between the results, a plausible explanation for the difference should be provided.

For statistical analyses other than those specified in this protocol, please refer to the statistical guidelines for clinical trials.

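### The formal hypotheses omit electroacupuncture versus no treatment, set a week with no scheduled visit, and measure the arms on different VAS outcomes

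*Protocol*

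**What the plan says.** All references are to the Protocol.

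- **Hypotheses (C. Number of participants).** Δ1 is acupuncture, Δ2 electroacupuncture and Δ3 no treatment. Two null hypotheses are listed: Δ1–Δ2 = 0, and "H0 : σ = Δ1 – Δ3 = 0". The sentence that opens the rationale says something else: that both active arms will improve relative to no treatment.
- **Definition of the changes (same section).** Δ2 is the "Mean change in VAS score of hand coldness at week 10 (within ±3 days) after randomization in the electroacupuncture group". Δ3 is worded the same way for the untreated arm. Δ1 has the same week but refers to coldness of the hands and feet.
- **Sample size (same section).** The two-mean formula is introduced with "The number of participants in the electroacupuncture treatment group and the no-treatment control group was set to be the same". It uses a single Type I error level of 0.05, and a β of 0.2, so 80% power.
- **Assessment times (Randomization Methods and Blinding).** "All three arms will be assessed for efficacy 5 weeks (±3 days) after randomization and followed up at 9 weeks (±3 days". The schedule tables give D35±3 for Visit 10 and D63±3 for Visit 11.
- **Primary outcomes (Clinical Protocol Overview).** Two are listed: the hand VAS and the "Visual Analog Scale (VAS) of coldhypersensitivity in the feet".
- **Analysis (How to analyze validity variables; General principles).** The change in VAS is compared between no treatment and acupuncture or electroacupuncture. The within-group change is Week 5 ±3 days minus Visit 1. Overall, "the significance level is 0.05 by two-sided test".

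**The concern.** The hypothesis block should fix which arms are compared, when, and on what measure. Here each of the three conflicts with the rest of the document.

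The missing contrast matters most. The trial is titled as a study of electroacupuncture, and a result for electroacupuncture against no treatment would answer no stated hypothesis. The two listed hypotheses do not supply it indirectly. If Δ2 = Δ3 and only Δ1 differs, both listed nulls are false while electroacupuncture is no better than no treatment.

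The week and the outcome matter because they define the primary estimate. Someone following the block literally would look for a week-10 value that no visit is scheduled to collect, and would subtract a hand score from a hands-and-feet score.

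Finally, two primary scales and more than one contrast share a single 0.05 level, while the sample size provides for one comparison on one scale.

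**Working it through.** **1. Contrasts, side by side**

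| Place | Acup. vs electroacup. | Acup. vs none | Electroacup. vs none |
|---|---|---|---|
| Opening sentence of the rationale | no | yes | yes |
| Formal hypotheses | yes | yes | **no** |
| Arms named in the sizing text | no | no | yes |
| Primary analysis text | not named separately | yes | yes |

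The formal list contains one contrast that the opening sentence lacks, and lacks one that it contains.

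**2. Time point**

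- Week 10 is day 70, so ±3 days is D67–73.
- Visit 10 is D35±3, or D32–38. Visit 11 is D63±3, or D60–66. Neither overlaps D67–73.
- The section on Visit 11 gives ±7 days, or D56–70. Its last days (D67–70) reach the window, but the nominal visit is still week 9.

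**3. Outcome**

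Hand and foot coldness are two separate 0–10 scales, and no combined score is defined. With Δ1 on hands and feet and Δ2 and Δ3 on hands, both listed differences mix measures.

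**4. What the sample size covers**

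Inputs: difference 1.04; SDs 1.03 and 1.17 from an oxygen-chamber versus placebo trial; two-sided 0.05 (1.96); power 80% (0.84).

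- Joint SD = √[(1.03² + 1.17²)/2] = 1.102.
- n = 2 × (1.96 + 0.84)² × 1.102² / 1.04² = 17.61, so 18 per arm. The stated 18 is reproduced.
- 18/(1 − 0.25) = 24 per arm, and 3 × 24 = 72.

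The printed formula shows SD 1.17, which would give 19.84, so 20 per arm. The stated result therefore rests on 1.102; this is a separate discrepancy.

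The calculation is for one two-group comparison on one VAS at 0.05. The 1.04 is the difference between an active device and placebo (1.52 − 0.48), so it carries no information on the difference between two active needling arms.

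**5. Error rate if every pairwise test were run ungated at 0.05**

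Two listed contrasts on two scales make 4 tests; adding Δ2–Δ3 makes 6. If independent, 1 − 0.95⁴ = 18.5% and 1 − 0.95⁶ = 26.5%. The tests share arms and the scales are correlated, so the rates were simulated under no effect (two-sample t-tests, 18 and 24 per arm). The Protocol gives no hand–foot correlation, so it is an assumption.

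| Assumed correlation | 4 tests | 6 tests | 6 tests, only after a significant three-group ANOVA on that scale |
|---|---|---|---|
| 0.3 | about 17% | about 22–23% | about 10% |
| 0.5 | about 16% | about 21% | about 9% |
| 0.7 | about 15% | about 20% | about 8% |
| 0.8 | about 14% | about 19% | about 8% |
| 1 | about 9% | about 12% | about 5% |

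Across correlations of 0.3–0.8 the ungated range is about 14–17% for four tests and 18–23% for six.

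**The case against.** A reader might infer that the trial cannot deliver its main claim. The documents do not support that. The rationale's opening sentence and the primary analysis text both plan electroacupuncture against no treatment, and the Overview compares all three groups. The fault may be one of labelling: if Δ1 had been the control arm, the two printed hypotheses would match the opening sentence exactly. Likewise week 10 may be a slip for Visit 10, which has the same ±3-day window, and the hand-only wording may come from translation. These explanations are plausible, but they are inferences, and the text that defines the primary comparison still needs correcting.

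A reader might also take the 14–23% as the trial's actual error rate. It is not established. The Protocol names ANOVA, repeated ANOVA and paired t-tests for the primary outcome, not ungated pairwise t-tests at 0.05, and an alpha rule may sit in a statistical analysis plan that is not at hand. An ANOVA gate on each scale would bring the six-test figure to about 10% or less. The Protocol states neither procedure, so the figures show only what would follow from one reading.

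Nor do the documents support a power figure for electroacupuncture over acupuncture, or for success on both scales. Each would need an effect, a correlation or a success rule that the Protocol does not give.

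It is also tempting to dictate the order of tests. The Primary purpose section can be read as asking what electroacupuncture adds to acupuncture, and the three-group comparison appears under Secondary purpose. The Overview lists hand and foot VAS equally. Ranking them is the sponsor's decision.

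**Conclusion.** The point holds as an internal contradiction in the rules that define the primary contrast, time point and outcome. It is wrong as written, and more than a clerical slip, because three defining elements of the primary comparison disagree with the design and analysis sections. The contradictions need no assumptions; they follow from reading the sections together.

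The planned 18 evaluable and 24 enrolled per arm are unaffected if one active-versus-no-treatment contrast on one VAS is placed first. The stated 80% power does not extend to Δ1–Δ2. The false-positive range is secondary and conditional: it assumes ungated pairwise tests and a hand–foot correlation of 0.3–0.8.

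**What to change.** 1. Restate the hypotheses to include Δ2–Δ3 alongside Δ1–Δ3.
2. Define every Δ as the change from Visit 1 to Week 5 (Visit 10, D35±3), on the same VAS in all arms, with hand and foot stated separately.
3. Reconcile the place of Δ1–Δ2 with the Primary purpose and Secondary purpose sections.
4. State that the sample size covers one active-versus-no-treatment contrast on one VAS at two-sided 0.05, and that it does not support 80% power for Δ1–Δ2.
5. Name one contrast and one VAS as first, and test the others in a fixed order. The sponsor chooses the order.

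The cost is wording only: no extra participants, with 72 in total unchanged. The downside is that later tests are confirmatory only if the earlier ones succeed.

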##### Primary purpose

The efficacy will be evaluated by comparing the change in Visual Analogue Scale (VAS) scores of coldhypersensitivity in the hands and feet after 15 minutes of acupuncture on acupuncture points (LI4-LR3, LR3-SP6), performed twice a week for a total of 10 acupuncture treatments, or by adding electroacupuncture to the same acupuncture points.

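### The protocol disagrees with itself on which contrast is primary and which is powered, and its one effect size (1.04) gives no support for acupuncture versus electroacupuncture

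*Protocol*

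**What the plan says.** Four places in the protocol bear on this.

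- **Primary purpose.** Efficacy is judged by the VAS change after acupuncture, "or by adding electroacupuncture to the same acupuncture points". The no-treatment group is first named under Secondary purpose.
- **C. Number of participants, hypotheses.** The first is "H0 : σ = Δ1 – Δ2 = 0" and the second is "H0 : σ = Δ1 – Δ3 = 0". Δ1 is defined as the acupuncture group, Δ3 as the untreated group, and Δ2 as "Mean change in VAS score from pre- treatment to post-treatment in the electroacupuncture group". As labelled, the pairs are acupuncture versus electroacupuncture and acupuncture versus no treatment. Yet the rationale opens by saying that both treatment groups are expected to improve relative to no treatment.
- **C. Number of participants, sizing.** In the referenced oxygen-chamber trial, "the mean VAS difference for the placebo group was -0.48 with a standard deviation of 1.03", and the oxygen-chamber group changed by -1.52 (SD 1.17). The protocol concludes: "The expected difference between acupuncture treatments for coldhypersensitivity in the hands and feet is 1.04". Just before the formula it adds: "The number of participants in the electroacupuncture treatment group and the no-treatment control group was set to be the same". The result is 18 evaluable and 24 enrolled, applied to all three arms.
- **How to analyze validity variables.** The primary between-group analysis is framed as no treatment against the acupuncture or the electroacupuncture group. Under General principles, "the significance level is 0.05 by two-sided test".

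**The concern.** Acupuncture and electroacupuncture are both active arms, needled at the same eight points to the same depth on the same schedule. They differ in the electrical stimulation. A difference observed between an active device and a placebo says nothing direct about how much that stimulation adds to needling. By calling 1.04 a difference between acupuncture treatments, and by placing acupuncture versus electroacupuncture first among the hypotheses, the protocol invites the reader to treat that contrast as adequately powered.

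What is at stake is interpretation. If the comparison is not significant, it could be reported as showing that electrical stimulation adds nothing, although the confidence interval may still include a worthwhile gain. In addition, the pair that was actually sized, electroacupuncture versus no treatment, has no formal hypothesis.

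**Working it through.** **Inputs from C. Number of participants:** changes of -0.48 (SD 1.03) and -1.52 (SD 1.17); α = 0.05 (two-sided, from General principles); β = 0.2; dropout 25%.

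**Step 1: reproduce the plan's figure.**
- Difference: 1.52 - 0.48 = 1.04.
- Pooled SD: √[(1.03² + 1.17²)/2] = √1.2149 = 1.102, as stated.
- n per arm = 2(1.96 + 0.84)² × 1.102² / 1.04² = 17.61, so 18. Enrolled: 18/(1 - 0.25) = 24.
- Power at 18 per arm and 1.04 is 80.8% by normal approximation and 78.5% by t-test.

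So 18 and 24 reproduce with SD 1.102. The printed formula shows 1.17, which would give 19.85 rather than the printed 17.625. That is a separate slip, and nothing below relies on it.

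**Step 2: which contrast does each place support?**

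| Place in the protocol | Contrast |
|---|---|
| Primary purpose | Ambiguous; can be read as electroacupuncture vs acupuncture |
| First hypothesis | Acupuncture vs electroacupuncture |
| Second hypothesis | Acupuncture vs no treatment |
| Opening of the rationale | Each active arm vs no treatment |
| Origin of 1.04 | Active vs placebo |
| Label given to 1.04 | Between acupuncture treatments |
| Pair named at the formula | Electroacupuncture vs no treatment |
| Primary analysis | Each active arm vs no treatment |

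These cannot all hold together.

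**Step 3: what the sizing assumption implies for the head-to-head contrast.** Write each effect as points of VAS improvement. Then

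(electroacupuncture - acupuncture) = (electroacupuncture - none) - (acupuncture - none).

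If electroacupuncture beats no treatment by 1.04, any benefit of acupuncture over no treatment leaves a head-to-head difference below 1.04. If instead acupuncture itself gains 1.04, electroacupuncture would have to gain 2.08 for the head-to-head difference to reach 1.04.

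**Step 4: power for the head-to-head contrast.** The documents give no difference, so 75%, 50% and 25% of 1.04 are assumed. A two-sample t-test is used with SD 1.102, two-sided α 0.05 and noncentrality δ/(SD√(2/n)). The standard error is 1.102 × √(2/18) = 0.367 with 18 per arm and 1.102 × √(2/24) = 0.318 with 24.

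| Assumed difference | 18 per arm | 24 per arm |
|---|---|---|
| 1.04 | 78.5% | 89% |
| 0.78 | 54% | 67% |
| 0.52 | 28% | 36% |
| 0.26 | 11% | 13% |
| Difference detectable at 80% power | 1.06 | 0.91 |
| 95% CI half-width | 2.032 × 0.367 = 0.75 | 2.013 × 0.318 = 0.64 |

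The 18-per-arm column is the planned evaluable number. The 24-per-arm column applies if everyone randomized is analysed, as the ITT main analysis with LOCF intends.

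**The case against.** The strongest reply is that the protocol never says in so many words that acupuncture versus electroacupuncture has 80% power. The rationale opens with both treatments against no treatment, the sizing names electroacupuncture and no treatment, and the primary analysis is framed the same way. On that reading, a borrowed active-minus-placebo value of 1.04 is an understandable planning figure, and the power statement was meant only for comparisons with no treatment. The primary purpose could mean evaluating either treatment, in line with the general objective. The label on 1.04 may be loose translation, and Δ1 may have been intended as the control arm.

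Much of this stands. A reader might infer that the head-to-head comparison is unambiguously the primary aim and is promised 80% power. The documents do not support that: they point both ways, and the same n is simply applied to each arm. A reader might also infer that a null head-to-head result is the expected outcome. That does not follow either. At an assumed 0.78, significance is more likely than not (54% or 67%), and at 1.04 power is near the planned value.

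The reply does not remove the contradiction. On its reading, the first listed hypothesis has no power calculation at all, the label on 1.04 is wrong, and the contrast that was sized is missing from the hypotheses. A mislabelled Δ1 is possible but cannot be shown from the text.

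**Conclusion.** The point holds as an internal contradiction and a mislabelled effect size. It is not an error in the arithmetic behind 18 per arm. The planned power is supported, on the protocol's own inputs, only for an active arm against no treatment (about 78.5% by t-test at 18 per arm with SD 1.102). Even there it assumes that a difference from placebo in another trial carries over to a difference from no treatment here.

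For acupuncture versus electroacupuncture the power is unsupported. The trial can reliably detect only an added effect of about 0.9 to 1.06 points, close to the whole effect borrowed from the oxygen-chamber trial. The lower power figures are conditional on assumed differences of 0.26 to 0.78, which the documents neither give nor exclude. This should be fixed, but it does not call the size of the trial into question for comparisons with no treatment.

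**What to change.** 1. In C. Number of participants, relabel 1.04 as the expected difference between an active arm and no treatment.
2. Reconcile the Primary purpose, the hypotheses, the sizing text and the primary analysis so that the primary hypotheses are acupuncture versus no treatment and electroacupuncture versus no treatment. The second must be added, because it is sized but not listed.
3. State that the planned power (about 78.5% by t-test at 18 per arm, SD 1.102) applies only to each of those two contrasts.
4. Make electroacupuncture versus acupuncture a secondary contrast, reported as an estimate with a 95% CI (expected half-width about 0.75 points at 18 per arm, 0.64 at 24). State that it is not powered and that a non-significant result will not be read as equal efficacy. Label any power figure quoted for it as resting on an assumed difference.

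The cost is a wording change in the objectives, sample-size and analysis sections, and a less favourable stated power for the head-to-head comparison. No extra participants are needed. If the sponsor wants the head-to-head comparison to be primary, it would have to justify a difference for that contrast and resize. At an assumed 0.52, for example, the normal approximation gives 71 evaluable, or 95 enrolled, per arm.
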